#### Guidelines for Drug Combination

(1) During the trial, expectorants, bronchodilators, and other Chinese and Western medicines with antitussive and expectorant effects are not allowed to be used. For example, salbutamol, ipratropium bromide, budesonide, acetylcysteine, terbutaline, ambroxol hydrochloride, which are western medicines commonly used for expectoration and bronchiectasis; and compound fresh bamboo juice, Feilike Mixture, cough syrup, which are Chinese patent medicine used to remove phlegm and relieve cough.(2) Antibiotics should not be given routinely. Whenever needed, antibiotics can be used under the doctor’s discretion, but the duration, dosage, and frequency should be recorded in detail.(3) When the axillary temperature exceeds 38.5°C during the study, physical cooling or antipyretic analgesics (e.g. ibuprofen suspension) can be used together, and usage information should also be recorded in detail.(4) The physician should ask the participants to bring all medication taken by themselves during the follow-up to check for combination medication. For the drugs or other treatments that must be taken continuously due to the combination of diseases, the name, duration, dosage, and frequency of the drugs must be recorded in the medical record, so as to facilitate the summary, analysis and reporting later.

#### Outcome Evaluation

##### Primary Outcome

The disappearance time of cough should be recorded daily, then evaluated at the study endpoint.

##### Secondary Outcome

(1) Area Under Curve (AUC) of cough and expectoration symptom score-time, cough symptom score (Table 3), antitussive onset time, clinical recovery time, and TCM syndrome score (Li, 2015) (Table 4) will be daily recorded and evaluated at the study endpoint.i. Cough disappeared: cough symptom score (daytime + night) ≤1 point, and maintained for 24 h or more.ii. Antitussive onset time: the number of days required for cough symptom score to decrease by one point after taking the medicine.iii. Clinical recovery: cough, expectoration and pulmonary symptoms are all mild after treatment, without affecting study, living and sleep.iv. Evaluation criteria for the efficacy of TCM syndromesA. Clinical recovery: the total score decreased by ≥90%.B. Significant effect: the total score decreased by ≥70% and <90%.C. Effective: the total score decreased by ≥30% and <70%.D. Ineffective: those who fail to meet the above standards.(2) The disappearance rate of cough, sputum and pulmonary rales will be evaluated at the study endpoint.(3) The usage of antibiotics, antipyretics or analgesics will be evaluated at the study endpoint.

**TABLE 3 T3:** Cough symptom scoring.

Score	Daytime symptom	Night symptom
0	No cough	No cough
1	Short occasional cough	Short occasional cough during sleep
2	Frequent cough, daily activities mildly affected	Slight disturbance of sleep due to cough
3	Frequent cough, daily activities severely affected	Severe disturbance of sleep due to cough

**TABLE 4 T4:** Quantitative Grading evaluation for TCM syndrome.

Grading symptoms		(−)	(+)	(++)	(+++)
Primary symptoms		0	1	2	3
Cough	Daytime	No cough	Short occasional cough	Frequent cough, daily activities mildly affected	Frequent cough, daily activities severely affected
	Night	No cough	Short occasional cough during sleep	Slight disturbance of sleep due to cough	Severe disturbance of sleep due to cough
Expectoration	Daytime	No expectoration	Phlegm is whitish and slightly sticky	Phlegm is whitish/yellowish and sticky	Phlegm is yellowish and sticky
	Night	No expectoration	Phlegm is easy to cough out	Phlegm is slightly difficult to cough out	Phlegm is difficult to cough out
Secondary Symptoms		0	1	2	3
Fever (24 h maximum axillary temperature)		≤37.2°C	37.3–37.9°C	38.0–38.5°C	>38.5°C
Thirsty		No	Yes	Yes	Yes
Facial Erythema		No	Yes	Yes	Yes
Dysphoria		No	Yes	Yes	Yes
Scanty dark-colored urine		No	Yes	Yes	Yes
Dry stool		No	Yes	Yes	Yes
Tongue and pulse condition		Normal	Abnormal	Others	
Tongue		Pinkish	Reddish	—	
Tongue coating		Thin whitish coating	Yellowish coating	—	
Pulse condition		Normal	Slippery and rapid	—	

Note : Children who cannot expectorate is not included.

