#### Inclusion Criteria

(1) Participants with AB under the diagnostic criteria of Western medicine.(2) Those who meet the TCM diagnostic criteria of phlegm-heat stasis in lungs.(3) Participants aged 2–14 years.(4) Cough (day + night) score ≥4 points.(5) Duration of disease ≤48 h, no antibiotics, antitussives, phlegm-reducing drugs, and other Chinese or Western medicine that influence cough has been used before treatment.(6) The informed consent process complies with the regulations, and the legal representative and/or the child (≥8 years old) signs the informed consent.

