#### Drop-Out Criteria

(1) Participants who develop an allergic reaction or serious adverse event (SAE) would be withdrawn from the trial according to the doctor’s judgment.(2) Participants with other concomitant diseases occurring during the trial, which affected the assessment of efficacy and safety of JZOL.(3) Participants whom have poor compliance, changed their medication midway, or added drugs prohibited under this study.(4) Any reason breaking the double-blind setting of this clinical trial.(5) After medication, if the total score of cough and expectoration increased by four points or the armpit temperature >38.5°C continued for more than 48 h, or the child developed bronchial pneumonia, the tested medication should be stopped immediately, effective treatment should be given. The child should complete all laboratory tests, be withdrawn from the study, and be considered an invalid case.(6) Participants who are found to have serious violations of inclusion or exclusion criteria after being enrolled in this study.

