### Statistical Analysis

SAS will be used for statistical analysis. Intention-to-treat analysis will be carried out in this trial, which refers to the analysis of all cases that have been randomized and used drugs at least once. All statistical tests are conducted using a two-sided test, and *p* <0.05 would be considered statistically significant. The missing data will be filled up by carrying forward the last measured value in this trial. Covariance analysis is used for the evaluation of the cough disappearance time. The group is taken as a fixed effect, and the baseline value of the cough symptom score is taken as covariance into the model for analysis. The difference between the different values of the two groups and their bilateral 95% confidence intervals are calculated. Then, the lower limit of bilateral 95% confidence intervals and the preset non-inferiority standard are compared to determine whether the test group is inferior to the control group. In addition, the subgroup analysis is performed according to age (2–3 years, 4–7 years, and 8–14 years). Measurement methods and data sets of secondary outcomes are shown in Table 5. In terms of safety, the number of AEs and SAEs during the study will be listed, and their incidence will be calculated.

**TABLE 5 T5:** Secondary outcome.

Secondary outcome	Test method	Data set
Time-lapse analysis of measured value and changed value of cough symptom score	T test is used to compare the differences between groups	FAS^a^
AUC of cough and expectoration symptom score - time		
Onset of cough relief		
Clinical recovery time		
Disappearance rate of cough, expectoration and lung rales	χ2 test or Fisher’s exact probability method is used to compare the differences between groups	
Use of antibiotics, antipyretics and analgesics		
Analysis on the curative effect of TCM syndrome	CMH chi-square is used to compare the differences between groups	

a FAS, Full Analysis Set; AUC, Area Under Curve.

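### Children who cannot expectorate are left out of Table 4 scoring but belong to the full analysis set, so the t test of the cough-and-expectoration AUC either pools two scale lengths or is not run in the set that Table 5 names

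*Protocol article*

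**What the plan says.** Inclusion Criteria: "Participants aged 2–14 years". Neither the inclusion nor the exclusion list mentions ability to bring up phlegm.

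Secondary Outcome lists "Area Under Curve (AUC) of cough and expectoration symptom score-time". Table 4 grades cough by day and by night at 0–3 each, and expectoration by day and by night at 0–3 each (daytime grade 1, for example, is "Phlegm is whitish and slightly sticky"). The table's closing note says "Children who cannot expectorate is not included". It does not say whether the item or the child is left out, or when ability is judged.

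Statistical Analysis, Table 5, places "AUC of cough and expectoration symptom score - time" under the t test, with the full analysis set as the data set. The text of that section defines the analysed cases as everyone randomised who took study drug at least once, with no exception for non-expectorators. Missing values are filled by carrying the last measurement forward.

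Two other places use expectoration. Clinical recovery requires that "cough, expectoration and pulmonary symptoms are all mild after treatment", and one Drop-Out criterion applies if "the total score of cough and expectoration increased by four points".

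**The concern.** A child who cannot expectorate can be enrolled, randomised and dosed, and so belongs to the full analysis set. Following the Table 4 note, that child has no expectoration score. The note and Table 5 cannot both be applied without a further rule. Carrying the last value forward does not supply one, because an item that was never scored has no last value.

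At stake is the precision and meaning of one secondary outcome. Either the AUC difference averages over two scale lengths, with the gap between them left in the error term, or the result describes a smaller population than the one named. There is also a recording problem. Grade 0 in Table 4 means no phlegm. If an inapplicable item is entered as 0, the data cannot later separate a child without phlegm from a child unable to bring it up.

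**Working it through.** **The plan's own figure.** The only computed figure is 417 per group for the primary outcome (SD 2, true difference 0, margin 0.5, one-sided 0.025, power 0.95). The normal approximation gives 2 × (1.960 + 1.645)² × 2² / 0.5² = 415.8, so 416. The exact t calculation gives 417 (power 0.9501; 416 gives 0.9496). It reproduces, and this point does not touch it: disappearance of cough is defined on cough alone ("cough symptom score (daytime + night) ≤1 point").

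**Scale ranges, from Table 4.** Cough: 2 items × 3 = 6. Cough plus expectoration: 4 items × 3 = 12. A child without the expectoration items has half the maximum daily score, and so half the maximum AUC.

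**Is the AUC a sum?** The article does not say so directly. The Drop-Out criterion's total of cough and expectoration supports that reading. If two separate AUCs are meant, no scales are mixed, but the expectoration AUC still cannot cover the full analysis set.

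**Illustration. All inputs here are assumed except 500 per arm.**
- 7-day AUC mean 14 for expectoration; SD 6 for each part; correlation 0.6; the same effect d on each part.
- q is the share of non-expectorators. If ages were uniform over 2–14, ages 2–3 would be 2/13 = 15.4% and ages 2–5 would be 4/13 = 30.8%. These only provide plausible values of q; the document gives none.
- d is chosen for 80% power on cough AUC alone: (1.960 + 0.842) × 6 × √(2/500) = 1.063.

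Formulas:
- Variance of the summed AUC = 36 + 36 + 2 × 0.6 × 36 = 115.2
- Within-status variance W = (1−q) × 115.2 + q × 36
- Variance from the scale gap B = q(1−q) × 14²
- Mean effect = d(2−q)
- Plain t test uses SD √(W+B); adjusting for status removes B.

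For q = 0.308: W = 90.8, B = 41.7, SD = 11.5, effect = 1.80.
- Unadjusted: 1.80 / (11.5 × 0.0632) = 2.47; power = Φ(2.47 − 1.96) = 0.695.
- Adjusted: 1.80 / (9.53 × 0.0632) = 2.99; power = Φ(1.02) = 0.847.

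| Share q | Unadjusted | Adjusted | Unadjusted, expectoration mean 8 |
|---|---|---|---|
| 10% | 82% | 87% | 85% |
| 15.4% | 78% | 86% | 84% |
| 30.8% | 70% | 85% | 79% |

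The last column repeats the calculation with B = q(1−q) × 8². The size of the loss depends strongly on the assumed expectoration mean.

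A separate set of assumptions gives the same direction. Take AUC mean 35, SD 12 and effect 0.2 SD, with non-scorers at half the mean and effect and 0.55 of the SD. Power is 88.5% with no non-scorers. At 10%, 20% and 30% it is 81%, 74% and 68% with mixed scales, or 85%, 81% and 75% if those children are dropped.

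**The Drop-Out criterion.** Entry requires a day-plus-night cough score of at least 4, and the cough maximum is 6. If the rise is counted from entry, a child scored on cough alone can rise by at most 6 − 4 = 2 points, so a four-point rise cannot occur. The criterion, the entry score and the Table 4 note do not fit together for these children.

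**The case against.** The strongest objection is one of detail. This is a condensed article, and the handling of an inapplicable item is often left to a case report form guide or an analysis plan that is not shown. That stands for the missing derivation rule. It does not remove the conflict between two statements the article does make: the exclusion in Table 4 and the full analysis set in Table 5.

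The size is also open to challenge, and rightly. Every mean, SD, correlation and effect is assumed, the plan claims no power for this outcome, and at 10% non-expectorators the mixed AUC still does slightly better than cough alone (82% against 80%).

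A reader might infer several stronger things that the document does not support:
- **That the youngest children are lost.** This is plausible, but neither the ages nor the number of non-expectorators is stated.
- **That the TCM grades and clinical recovery fail in the same way.** The TCM grade is a percentage fall in each child's own total, so consistent omission of the item leaves it usable. Recovery can be judged on the remaining components.
- **That phlegm loosening under treatment moves a child from unscored to scored, so that improvement raises the AUC.** Table 4 already grades phlegm that is difficult to bring up, so the note more naturally means children who cannot expectorate at all. Nothing says ability is judged again during treatment.
- **That the comparison is biased.** Allocation is double-blind and stratified by age. If only the item is omitted and status does not change, the t test stays valid.

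The opposite reading, that such children are never enrolled, has no support in the eligibility criteria.

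**Conclusion.** The point holds as a limited one. The Table 4 note and the Table 5 analysis set conflict for the cough-and-expectoration AUC. The consequence is lost precision and a blurred estimand if the item is omitted, or a population other than the one named if the child is omitted. The mixed-scale version depends on the AUC being a summed score, which is inferred.

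The loss cannot be computed from the document. On the main assumed inputs it is about 5 percentage points of power at 10% non-expectorators and 15 at 31%. With an expectoration mean of 8 it is about 2 and 5 points. The change is worth making because it costs little and status is hard to recover once the diaries are filled in.

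**What to change.** - Record ability to expectorate once, at baseline, and keep that status for all later scoring.
- Reword the Table 4 note to say that the item is omitted and the child is not.
- In Table 5, analyse the combined AUC in the full analysis set with baseline expectoration status as a factor, in place of the plain t test.
- Report cough AUC in the full analysis set, and expectoration AUC in children able to expectorate at baseline, as supporting results. The combined difference remains an average over two kinds of children, and these two results show what lies behind it.
- Compute the TCM percentage change from the same items at both time points.
- Reconcile the Drop-Out criterion on the cough-and-expectoration total with the entry cough score and the Table 4 note. Which clinical rule should apply is for the investigators and sponsor.

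Cost: one yes/no item on the baseline form and wording in Tables 4 and 5, with no added patients or visits. The expectoration AUC will cover fewer children than the full analysis set.

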### Safety Evaluation

General physical examination, such as body temperature, pulse rate, respiration and blood pressure, are measured at baseline, during the treatment period and at the end of the treatment. Routine blood investigations, urinalysis, stool routine tests, liver function tests, renal function tests and ECG are examined at baseline and at the end of the trial. Participants who are normal before treatment but abnormal after treatment should be re-examined regularly until the end of follow-up. Possible AEs and allergic reactions will be observed at any time after medication. If an AE occurs during the trial, the sponsor shall be responsible for the cost of treatment until the AE disappears or the condition becomes stable.

### Mechanism Investigation

In order to understand the mechanism of the action for efficacy of JZOL in the treatment of AB, stool, saliva and blood are collected three times, i.e., before treatment, 5 days after treatment and at the end of treatment, followed by stool/saliva metagenomics analysis and stool/blood metabolomics analysis. In order to exclude the effect of antibiotics on the intestinal flora and its metabolites, participants who received antibiotics during treatment should be excluded.

### Quality Control

In order to ensure the quality of the trial and the implementation of quality assurance system, investigators are required to carry out clinical trials according to standard operating procedures (SOPs). All the results and findings in the trial should be verified to ensure the reliability of the data and to ensure that the conclusions of clinical trials are derived from the original data. Researchers must carry out quality control at every stage of data processing to ensure that all data are reliable and processed correctly.

This trial will carry out quality control in the following aspects: progress of the trial; qualification of clinical sub-center; qualification of researchers; mastery of procedures; scientificity, authenticity, accuracy, and completeness of CRF; preservation of files; program implementation; AEs; preservation and storage of drugs; collection and management of biological samples; written informed consent; patients compliance; and laboratory examination data. In particular, the authenticity and accuracy of the CRF, the implementation of the program, and the determination of AEs will be strictly inspected. A diary record card for this trial will be provided to record medication status, symptom and syndrome score. In this way, recall bias can be avoided and study quality and compliance can be improved.

Before the drafting of the protocol, the study will invite experts in the pediatric and respiratory fields to hold a design meeting to determine the test objectives, ideas, and methods. After the protocol is drafted, all study sub-centers will be convened to discuss specific operation details and enhance the operability of the protocol. After the protocol is drafted, all study sub-centers will be convened to discuss specific operation details and enhance the operability of the protocol. During the implementation of the trial, research training sessions will be held in each clinical sub-center to strengthen the researchers’ and quality control staff’s grasp and understanding of the trial scheme and its key procedures. At the same time, interim coordination meetings will be convened as appropriate to discuss and solve technical problems in the operation process. After the completion of the trial, all clinical sub-centers will be invited to participate in the trial summary meeting to discuss the Multi-center Summary Report.

### Data Management

Electronic data management and direct-attached storage for Electronic Data Capture (EDC) system are used in this study. The Data Management Plan (DMP) is written by the data manager as the guidance for data management and is approved by the sponsor. The data management will be carried out in accordance with the time, content, and method defined by the DMP. The integrity of the data will be checked by reviewing whether all paper and electronic materials are filled in and archived following SOPs. The authenticity of participants will be checked by telephone follow-up. Paper materials of the data will be collected after passing the review by composition of data monitoring committee. Researchers responsible for data input will log in to the established EDC and enter data into eCRF in the principle of double-person and double-enter, and conduct consistency tests to ensure the accuracy of the data.

### Statistical Analysis

SAS will be used for statistical analysis. Intention-to-treat analysis will be carried out in this trial, which refers to the analysis of all cases that have been randomized and used drugs at least once. All statistical tests are conducted using a two-sided test, and *p* <0.05 would be considered statistically significant. The missing data will be filled up by carrying forward the last measured value in this trial. Covariance analysis is used for the evaluation of the cough disappearance time. The group is taken as a fixed effect, and the baseline value of the cough symptom score is taken as covariance into the model for analysis. The difference between the different values of the two groups and their bilateral 95% confidence intervals are calculated. Then, the lower limit of bilateral 95% confidence intervals and the preset non-inferiority standard are compared to determine whether the test group is inferior to the control group. In addition, the subgroup analysis is performed according to age (2–3 years, 4–7 years, and 8–14 years). Measurement methods and data sets of secondary outcomes are shown in Table 5. In terms of safety, the number of AEs and SAEs during the study will be listed, and their incidence will be calculated.

**TABLE 5 T5:** Secondary outcome.

Secondary outcome	Test method	Data set
Time-lapse analysis of measured value and changed value of cough symptom score	T test is used to compare the differences between groups	FAS^a^
AUC of cough and expectoration symptom score - time		
Onset of cough relief		
Clinical recovery time		
Disappearance rate of cough, expectoration and lung rales	χ2 test or Fisher’s exact probability method is used to compare the differences between groups	
Use of antibiotics, antipyretics and analgesics		
Analysis on the curative effect of TCM syndrome	CMH chi-square is used to compare the differences between groups	

a FAS, Full Analysis Set; AUC, Area Under Curve.

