### Sample Size Calculation

In this study, the disappearance time of cough is used as the primary outcome. According to previous studies, the disappearance time of cough in the experimental group and the control group is about 5 ± 2 days. The non-inferiority threshold of this study is set as 0.5 days, unilateral α = 0.025, power = 0.95, and the PASS (V14.0) is selected to estimate the sample size. Based on the calculation, 417 cases are needed for each group. After considering the proportion of withdrawals, the sample size of this study is 500 cases for each group, with a total of 1000 cases.

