### Intervention Method

The Intervention group takes JZOL and AHCHOS placebo, while the control group receives AHCHOS and JZOL placebo. Both drugs and their placebos are taken orally. According to different ages and weights, the dosages of the two drugs are shown in Table 1. The conditions treated by the two drugs in this study are the same as publicly available information. Ibuprofen Suspension will be taken when two groups of participants appear in an emergency. The medication lasts for 7 days. The treatment medicine and their placebos are provided by Jiangsu Kanion Pharmaceutical Co., Ltd according to the double-blind principle. The schedule of enrollment, interventions, and assessments is shown in Table 2.

**TABLE 1 T1:** Usage instructions for both drugs.

Jinzhen oral liquid and its placebo		
**Age**	**Dosage**	
2–3 years old	10 ml each time, twice a day	
4–7 years old	10 ml each time, three times a day	
8–14 years old	15 ml each time, three times a day	
Ambroxol Hydrochloride and Clenbuterol Hydrochloride Oral Solution and its placebo		
** Age**	**Weight**	**Dosage**
** 2–3 years old**	12–16 kg	7.5 ml each time, twice a day
** 4–5 years old**	16–22 kg	10 ml each time, twice a day
** 6–12 years old**	22–35 kg	15 ml each time, twice a day
** More than 12 years old**	—	20 ml each time, twice a day

Note: In case of inconsistency between age and weight, the dosage can be adjusted according to their weight.

**TABLE 2 T2:** Flow chart for clinical trial.

Stage procedure	Screening stage /Baseline (1st Visit)	During treatment (2nd Visit)<	After treatment (3rd Visit)
	−1 ∼ 0 days	5 ± 1 day	7 ± 1 day
Patient screening	×	—	—
Sign informed consent form	×	—	—
Fill in demographic information	×	—	—
Past medical history	×	—	—
Medical comorbidities and current medication	×	—	—
Chest radiograph	×	—	—
General examination	×	×	×
Physical examination	×	×	×
TCM syndrome scoring and grading	×	×	×
Routine blood investigations, urinalysis and stool examination	×	—	×
Liver function tests (ALT, ALP, AST, TBIl, γ-GT) and kidney function tests (BUN, Cr)	×	—	×
ECG	×	—	×
Stool/salivary metagenomic analysis	×	×	×
Stool/blood metabolomics analysis	×	×	×
Distribution and withdrawal of the remaining intervention medication	×	—	×
Distribution and withdrawal of patients’ medication diary record cards	×	×	×
Adverse events record	—	×	×
Combination therapy medication record	—	×	×
Conclusion (Trial Summary)	—	—	×

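### Carrying the last value forward does not fit cough disappearance time or daily cough scores, and cannot be relied on as conservative for non-inferiority

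*Protocol article*

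**What the plan says.** All statements are in the protocol article.

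- **Missing data (Statistical Analysis):** "The missing data will be filled up by carrying forward the last measured value in this trial". No outcome is exempted and no other rule appears.
- **Primary analysis (Statistical Analysis):** "Covariance analysis is used for the evaluation of the cough disappearance time", with group as a fixed effect and baseline cough score as covariate.
- **Population (Statistical Analysis):** "the analysis of all cases that have been randomized and used drugs at least once". Early leavers therefore stay in.
- **Primary outcome:** "The disappearance time of cough should be recorded daily, then evaluated at the study endpoint".
- **Event definition (Secondary Outcome, item i):** "cough symptom score (daytime + night) ≤1 point, and maintained for 24 h or more".
- **Follow-up:** "The medication lasts for 7 days" (Intervention Method). Table 2 puts the last visit at day 7 ± 1.
- **Sample size:** "the disappearance time of cough in the experimental group and the control group is about 5 ± 2 days", with margin 0.5 days, one-sided α 0.025, power 0.95 and 417 per group. Then: "After considering the proportion of withdrawals, the sample size of this study is 500 cases for each group". The withdrawal proportion itself is not given.
- **Drop-Out Criteria, item 5:** children whose cough and expectoration score rises by four points, whose fever persists or who develop bronchial pneumonia leave the study and are labelled invalid cases. No analysis value is attached to that label.
- **Table 5:** the cough score over time, AUC, onset time and recovery time are compared by t test in the full analysis set.

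**The concern.** Carry-forward needs an earlier value of the same quantity. A time to an event has none until the event happens, so the rule can only act on the daily scores from which the time is built. There it treats two kinds of leaver differently. A child last scored 2 or more stays above the threshold for ever and gets no time. A child last scored 1 or less may be credited with a sustained disappearance that nobody observed.

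For the daily scores and the AUC, the rule holds a score constant in an illness expected to resolve in about five days. It then analyses the filled-in days as if they had been recorded.

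The primary test is non-inferiority with a 0.5-day margin. Filled-in values that carry no arm difference pull the arms together, which favours a non-inferiority claim. Withdrawal is also linked to worsening, so the children affected are not a random subset.

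**Working it through.** **1. The plan's own sample size.** Inputs: SD 2, margin 0.5, true difference 0, one-sided α 0.025, power 0.95.
n = 2 × (1.960 + 1.645)² × 2² / 0.5² = 415.8, so 416 by the normal approximation. The noncentral t gives 417 (power 0.9501). The stated 417 reproduces. The allowance implied by 500 is 1 − 417/500 = 16.6%, or 83 children per arm. This is inferred; the article states no rate.

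**2. What the rule does to the primary outcome.**

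| Last observed day + night score | After carry-forward | Result |
|---|---|---|
| 2 or more | Stays at 2 or more | No disappearance time. ANCOVA must drop the child, against the stated population, or use an unstated number |
| 1 or less, not yet held for 24 h | Copied to the next day | 24 h condition met by an imputed value, if the rule is applied to diary days before the time is derived |
| 1 or less, already held for 24 h | Irrelevant | Time was observed |

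**3. How many leavers fall in each row (illustration).** The article gives no dropout pattern, so this simulation rests on assumptions: time Normal(5, 2) rounded to days, eight diary days, last observed day uniform over days 1–7 and unrelated to outcome, and a daily chance of 0–20% of a one-day dip to 1 or less before true disappearance.

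- 48–57% of leavers had no time after carry-forward.
- 13–20% had a time confirmed only by imputed scores. That time was false in 0% (no dips) to 7.5% (20% dips) of leavers.
- The rest already had an observed time.

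**4. Effect on the non-inferiority error.** Let q be the share of each arm holding an imputed time with no arm difference (assumption). A true deficit of 0.5 days then appears as 0.5 × (1 − q). With SD 2 and 500 per arm, SE = 2 × √(2/500) = 0.1265, and
P(false non-inferiority) = Φ(0.5 × q / 0.1265 − 1.96).

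| q | How obtained | Error |
|---|---|---|
| 0 | Nominal | 2.5% |
| 1.2% | 7.5% of 16.6% (false times only) | 2.8% |
| 2.2% | 13% of 16.6% | 3.0% |
| 3.3% | 20% of 16.6% | 3.4% |
| 5% | Illustrative | 3.9% |
| 10% | Illustrative | 5.9% |
| 16.6% | Entire allowance | 9.6% |

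The rows at 2.2% and 3.3% match the mechanism in step 2, since only children given a time by imputation can dilute the difference.

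**5. Direction.** A child withdrawn for worsening carries a high score, which counts against that child's own arm on AUC. On the primary outcome the same child has no time. Dropping the child removes a failure and flatters the arm; assigning a late value does the opposite. A child who leaves while recovering is denied further improvement. The sign depends on who leaves which arm.

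**The case against.** **The large error figure.** A reader might infer that false non-inferiority rises to 9.6%. The documents do not support that. It needs all 83 children per arm to hold a filled-in time with no arm difference, whereas many leavers get no time at all. The 16.6% is inferred from 417 and 500, and withdrawal is not the same as a missing primary outcome: with a mean of 5 days and 7 days of treatment, a child can leave after the cough has gone. This objection stands.

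**Anti-conservative throughout.** A reader might infer that the rule always favours non-inferiority. It does not: high scores carried from worsening children can count against their own arm. Non-inferiority also applies only to the primary outcome; Table 5 tests the secondary outcomes for differences. This stands too.

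**Confirmation.** The text does not say that carry-forward precedes derivation of the time. A day + night score could also be read as spanning 24 hours by itself. The unobserved confirmation is therefore conditional on one reading.

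**Censoring is a separate matter.** With Normal(5, 2), 15.9% of children pass day 7 without the event even with complete diaries (30.9% at day 6, 6.7% at day 8). A missing time is thus not solely a carry-forward problem, and an unseen analysis plan may hold a censoring rule. That is fair, but carry-forward is a rule the article states, for all missing data, so its misfit is not an omission.

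**Conclusion.** The point holds as a stated rule that does not fit the endpoints it governs. Three parts follow from the article alone: no disappearance time for a child who leaves with a score of 2 or more; daily scores and AUC frozen at dropout and treated as observed, which understates uncertainty (by an amount not quantified here); and missingness tied to outcome through the Drop-Out Criteria. The unobserved 24 h confirmation holds only if the rule is applied to diary days.

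The direction of bias is not fixed, so the rule cannot be relied on as conservative for non-inferiority. That is weaker than saying the 2.5% error rate is known to fail. The size is unknown. Under the assumptions shown, 2–3% of each arm with imputed times gives about 3.0–3.4%, and 9.6% is an upper illustration for this mechanism. One-arm scenarios can be made much worse: times 1–3 days too early in 2–8.3% of the JZOL arm alone would bias the difference by 0.02–0.25 days and give errors of 3.6–50%. Nothing in the article indicates such an imbalance. The sample size of 417 is not in error, and this point implies no corrected number. The change should be made before unblinding.

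**What to change.** Delete carry-forward as the general rule and replace it as follows.

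1. **Primary time.** Derive it from observed diary days only, with no imputed confirmation, and state what record satisfies the 24 h condition.
2. **Primary estimator.** Censoring cannot be done inside the stated ANCOVA, so choose one of two routes. (a) Treat children without observed disappearance as censored and estimate the arm difference in days, for example as restricted mean time to the end of follow-up adjusted for baseline cough score, against the 0.5-day margin. (b) Keep the ANCOVA with multiple imputation of the missing times. Under (a), confirm that the margin still suits a mean restricted to the follow-up period.
3. **Children withdrawn for worsening.** Censoring them is informative. State their analysis value, for example no disappearance by the end of follow-up, and reconcile the invalid-case label with the stated population. This concerns the analysis only, not when treatment stops.
4. **Sensitivity.** Add a tipping-point analysis that imputes progressively later disappearance for withdrawn JZOL children until the non-inferiority conclusion changes.
5. **Daily scores and AUC.** Use a mixed model for repeated measures, or multiple imputation from baseline score, age stratum and earlier diary days.

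Cost: analysis-plan wording, programming, a restated primary estimator and slightly wider intervals. No new data are needed, since the diary already records daily scores.
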